### Statistical analyses

The primary outcomes are AAA growth, AAA rupture and all-cause mortality. AAA growth will be based on multiple measurements and will therefore be analysed with a repeated measures analysis. Potential associations between AAA growth and risk factors that are also measured on multiple time points can be assessed with multivariable mixed-effects models, while potential associations between AAA rupture and risk factors can be tested with a conditional dynamic prediction model with landmarking, or with joint models in which linear mixed-effects models are combined with Cox regression.

Due to the expected multifactorial aspect of AAA growth, even weak correlations are of interest to detect. To that end, at least 750 patients are required to be able to detect a correlation coefficient of 0.16 with a power of 80% and a significance level of 0.05.

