## Methods and analysis

### Study design

The AAA bank is a prospective multicentre observational biobank, databank and imagebank of patients with AAA in The Netherlands (see table 1 for the WHO Trial Registration Data Set).

**Table 1 T1:** WHO trial registration data set

Primary registry and trial identifying number	ClinicalTrials.gov: NCT03320408
Date of registration in primary registry	25 October 2017
Secondary identifying numbers	NL59991.018.17, PARIS study, biobank Pearl AAA
Sources of monetary of material support	AMC Foundation for monetary support.
Primary sponsor	Academic Medical Center – University of Amsterdam
Secondary sponsor(s)	None
Contact for public queries	[name], [contact],[name], [name].
Contact for scientific queries	Principal investigator: [name], [contact],[name], [name]. [name], [contact],[name], [name].
Public title	PARIS study and biobank Pearl AAA
Scientific title	Predicting aneurysm growth and rupture with longitudinal biomarkers (PARIS study) and biobank Pearl AAA.
Countries of recruitment	The Netherlands
Health condition(s)	Abdominal aortic aneurysm
Intervention(s)	None
Key inclusion and exclusion criteria	Inclusion criteria: adult with an AAA or who has been previously treated for an AAA. Adequate comprehension of the Dutch language to provide written informed consent. Exclusion criteria: decisionally impaired patients. The exception are patients who are decisionally impaired due to the effects of an acute AAA for whom a separate recruitment and consent procedure exists.
Study type	Observational longitudinal patient registry and biobank
Date of first enrolment	4 October 2017
Sample size	Planned: 750 Currently enrolled: 161
Recruitment status	Recruiting; participants are currently being recruited and enrolled
Primary outcome(s)	Outcome: AAA growth. Time frame: up to 10 years of follow-up. Outcome. AAA rupture. Time frame: up to 10 years of follow-up. Outcome: all-cause mortality. Time frame: up to 10 years of follow-up. Outcome: evolution of serum levels of proteases and cytokines. Time frame: a maximum of 1 measurement annually up to 10 years of follow-up. Outcome: proteases and cytokine levels in AAA tissue. Time frame: if open AAA repair is performed and AAA tissue is collected. This is a one-time measurement.

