## Ethics and dissemination

The Medical Ethics Board and the Biobank Ethics Board of Amsterdam UMC (University of Amsterdam) have approved the AAA bank together with the PARIS study (table 5) within the scope of the Dutch Medical Research Involving Human Subjects Act (WMO) under registration number NL59991.018.17.

**Table 5 T5:** The PARIS study, the first proposed study that will be facilitated by the AAA bank

Aims	The aims of the PARIS study are: (1) to determine the association between AAA progression (growth or rupture) and the evolution of serum levels of both proteases and cytokines, (2) to determine the association between overall survival and the evolution of serum levels of proteases and cytokines, (3) to determine the association between serum levels of proteases and cytokines and level of proteases and cytokines in AAA tissue and finally (4) to determine the incidence of and characterise the type of complications after AAA repair.
Outcomes	The primary outcomes are: AAA growth, AAA rupture, all-cause mortality, serum levels of cytokines and proteases and cytokine and protease levels in AAA tissue. Secondary outcomes are the incidence and type of complications after AAA repair.
Sample size	Because of the multifactorial aspect of AAA progression, we calculated a sample size that will be sufficient for detecting weak correlations between cytokine and protease levels and AAA growth. To detect a correlation coefficient of 0.16 with a power of 80%, and a significance level of. 05, a sample size of 750 participants is required. Strategies to achieve sufficient participant enrolment include simple eligibility criteria and the expressed intention to extend the number of participating centres.

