Statistical analysis	Categorical variables will be presented as numbers and percentages and will be compared between groups with the χ^2^ test of Fisher’s exact test where appropriate. Continuous variables will be presented as means±SD or as medians with the IQR, depending on distribution. Distribution of continuous variables will be tested with the Shapiro-Wilk test. Continuous variables will be compared between groups with either the unpaired t-test or the Mann-Whitney U test depending on distribution. Individual AAA growth (based on repeated AAA diameter measurements) and the evolution of serum levels of cytokines and proteases will each be analysed with linear mixed-effects models to estimate the slope of temporal change (ie, the evolution through time). The linear mixed-effects model that estimates the slope for the evolution of each biomarker will also adjust for potentially relevant covariables including but not limited to sex, age and cardiovascular comorbidity. A forward stepwise selection will be used to select only those covariables that were significant in univariable analysis. Finally, correlations coefficient will be estimated between the slope of AAA progression and the slope of each biomarker. Freedom from AAA rupture and all-cause mortality will be estimated with the Kaplan-Meier method, while joint modelling will be used to assess the association between the evolution of serum levels of proteases and cytokines and AAA rupture and all-cause mortality. A joint model will be performed per biomarker. In order to assess the association, joint modelling combines linear mixed-effects models for the estimation of slope of temporal change per biomarker with Cox regression for the analysis of freedom from AAA rupture and all-cause mortality, in order to estimate HRs. The estimated slope and value of the studied biomarker will be added as covariables in each joint model. Furthermore, both models will be adjusted for potentially relevant covariables, including but not limited to sex, age, most recent AAA diameter and cardiovascular comorbidity using the same selection procedure. In addition, AAA growth instead of the most recent AAA diameter will be analysed in a separate multivariable joint model. In all analyses, a p value of <0.05 will be considered statistically significant, including the covariable selection procedure.

AAA, abdominal aortic aneurysm; PARIS, Predicting aneurysm growth and rupture with longitudinal biomarkers.

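### The sample size of 750 does not follow from its stated inputs: a correlation of 0.16 at 80% power and two-sided 0.05 needs about 305 analysed patients

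*Protocol article*

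**What the plan says.** The sample size is justified in two places. Under Statistical analyses, the article says that "at least 750 patients are required to be able to detect a correlation coefficient of 0.16 with a power of 80" per cent, and completes the inputs "with a power of 80% and a significance level of 0.05". In Table 5 (PARIS study, Sample size row) the aim is a number "sufficient for detecting weak correlations between cytokine and protease levels and AAA growth". The same inputs follow: "To detect a correlation coefficient of 0.16 with a power of 80" per cent, at the same significance level, "a sample size of 750 participants is required". Table 1 carries the figure as the enrolment target: "Planned: 750 Currently enrolled: 161".

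The Statistical analysis row of Table 5 bears on the calculation in two ways. It names the quantity to be tested: "correlations coefficient will be estimated between the slope of AAA progression and the slope of each biomarker". It also fixes the significance threshold: "In all analyses, a p value of <0.05 will be considered statistically significant, including the covariable selection procedure".

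Neither statement of the sample size mentions a loss rate, a number analysed, an adjusted alpha, a number of predictors or a reliability factor. Neither says whether the test is one- or two-sided.

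**The concern.** The effect size, power, alpha and sample size are all printed, and 750 is presented as what the other three require. A reader can therefore check the figure directly, and it does not come out.

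This is the only sample size justification in the article, and it supports the enrolment target. As printed, one of the four numbers is wrong or a step is missing, and the reader cannot tell which. The possible explanations mean different things. If the target correlation was nearer 0.10, the effect size is misstated. If about 305 analysed patients were meant to come out of 750 enrolled, a large loss has been assumed without being stated. If alpha was lowered for many biomarkers, that conflicts with the 0.05 printed for every analysis. Each reading gives a different answer to how many analysed participants the PARIS correlation analysis needs.

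**Working it through.** **Inputs.** Correlation r = 0.16, power 80% and alpha 0.05, all from Statistical analyses and Table 5. Sidedness is not stated, so both were tried, with two-sided as the main case.

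**Reproducing the stated figure.** For a test of zero correlation on the Fisher z scale,

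n = ((z_alpha + z_power) / atanh(r))² + 3, with atanh(0.16) = 0.1614.

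- Two-sided: ((1.960 + 0.842) / 0.1614)² + 3 = 304.35, so 305.
- One-sided: ((1.645 + 0.842) / 0.1614)² + 3 = 240.4, so 241.

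The stated 750 is not reproduced; 750 / 305 is about 2.5. One-sided testing widens the gap.

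**Does another test give 750?** These keep r = 0.16, 80% power and two-sided 0.05 unless noted.

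| Variant | Required n |
|---|---|
| Noncentral t instead of Fisher z | 301 |
| Rank correlation (variance factor 1.06) | 323 |
| Power 90% / 95% / 99% | 407 / 502 / 709 |
| F test of R² = 0.16² with 10 / 20 predictors | 628 / 814 |
| Difference of 0.16 on the Fisher z scale between two groups' correlations, total | about 1,212 |

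The first two use only the stated inputs and stay close to 305. The others change the power or the test, and none gives 750.

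**What 750 would deliver.** If all 750 entered a simple correlation test:

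- Power for r = 0.16: Φ(0.1614 × √747 − 1.960) = Φ(2.451) = 0.993.
- Correlation detectable with 80% power, two-sided: tanh(2.802 / √747) = 0.102 (one-sided 0.091). A target of exactly 0.10 would need 783.

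**What allowance would bridge the gap?** Each is taken alone, with the other inputs as printed.

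- Non-evaluable participants: 1 − 304.35/750 = 0.594, so about 59% of those enrolled.
- Multiplicity: the alpha giving 80% power at 750 is 2 × (1 − Φ(0.1614 × √747 − 0.842)) = 0.00036, and 0.05 / 0.00036 is about 140 tests. Bonferroni for 10, 20, 100 and 200 tests gives 515, 577, 721 and 782.
- Measurement error in the slopes: the observed correlation would have to shrink by a factor of 0.102 / 0.16 = 0.64. This would happen if each slope had reliability of about 0.64.

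The article states none of these.

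**The case against.** The strongest reply is that the article condenses a longer protocol, and that 750 may contain a sensible allowance described there. This is plausible. Previously repaired patients are eligible (Study population), patients may stop surveillance (Study procedures), surveillance samples are taken at most once a year (Table 4), and the planned correlation is between two estimated slopes. Losses and attenuation are to be expected. The reply explains how 750 might have arisen, but not the sentence as printed, which attributes 750 to three inputs that do not produce it. The complaint is not that detail was left out.

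A second reply is that the discrepancy is on the safe side. For the simple correlation test that is right and it stands: the stated inputs need fewer patients than planned, and the study is observational with no research visits.

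A reader might go further than the documents allow in three ways:

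- That 305 patients would be enough and the study is recruiting too many. The 305 applies to an observed correlation of 0.16 in a simple test. Noise in the estimated slopes shrinks the observed correlation below the true one, and several biomarkers will be tested.
- That the design has 99.3% power. This needs all 750 to be evaluable and the observed correlation to be 0.16, so it is an upper bound.
- That 750 is the wrong number. The documents show only that the four printed numbers are inconsistent, not which one is at fault or what the sponsor's full calculation contains.

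**Conclusion.** The point holds. With r = 0.16, 80% power and alpha 0.05, the requirement is about 305 analysed patients two-sided or 241 one-sided, against 750 stated, and no stated allowance accounts for the difference. If all 750 were analysed in a simple correlation test, power for 0.16 would be at most about 99.3%, and 80% power would be reached at a correlation of about 0.102.

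These figures rest on the usual Fisher z approximation for one correlation coefficient; the noncentral t version gives 301, so the choice between them does not matter. Because the discrepancy is conservative for this test, it does not call for a change in enrolment. It should still be corrected, because it is the study's only sample size justification and is wrong as written in two places.

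**What to change.** Change the sentence under Statistical analyses and the Sample size row of Table 5 in the same way, by one of two routes:

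1. Correct whichever of the correlation, power, alpha or sample size is misstated. For example: *750 analysed participants give 80% power to detect an observed correlation of about 0.102 at two-sided 0.05; an observed correlation of 0.16 needs about 305 analysed participants.*
2. If 750 includes an allowance for non-evaluable participants, multiplicity or measurement error in the slopes, state that allowance, the alpha used and the resulting number analysed. If the allowance is for multiplicity, the rule in Table 5 that sets 0.05 for all analyses must be reconciled with it.

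Either way, state whether the test is two-sided and whether the number means enrolled or analysed. The cost is two sentences, with no additional patients or procedures.

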### Patient and public involvement

This research was done without patient involvement. Patients were not invited to comment on the study design and were not consulted to develop patient relevant outcomes or interpret the results. Patients were not invited to contribute to the writing or editing of this document for readability or accuracy.

## Ethics and dissemination

The Medical Ethics Board and the Biobank Ethics Board of Amsterdam UMC (University of Amsterdam) have approved the AAA bank together with the PARIS study (table 5) within the scope of the Dutch Medical Research Involving Human Subjects Act (WMO) under registration number NL59991.018.17.

**Table 5 T5:** The PARIS study, the first proposed study that will be facilitated by the AAA bank

Aims	The aims of the PARIS study are: (1) to determine the association between AAA progression (growth or rupture) and the evolution of serum levels of both proteases and cytokines, (2) to determine the association between overall survival and the evolution of serum levels of proteases and cytokines, (3) to determine the association between serum levels of proteases and cytokines and level of proteases and cytokines in AAA tissue and finally (4) to determine the incidence of and characterise the type of complications after AAA repair.
Outcomes	The primary outcomes are: AAA growth, AAA rupture, all-cause mortality, serum levels of cytokines and proteases and cytokine and protease levels in AAA tissue. Secondary outcomes are the incidence and type of complications after AAA repair.
Sample size	Because of the multifactorial aspect of AAA progression, we calculated a sample size that will be sufficient for detecting weak correlations between cytokine and protease levels and AAA growth. To detect a correlation coefficient of 0.16 with a power of 80%, and a significance level of. 05, a sample size of 750 participants is required. Strategies to achieve sufficient participant enrolment include simple eligibility criteria and the expressed intention to extend the number of participating centres.
Statistical analysis	Categorical variables will be presented as numbers and percentages and will be compared between groups with the χ^2^ test of Fisher’s exact test where appropriate. Continuous variables will be presented as means±SD or as medians with the IQR, depending on distribution. Distribution of continuous variables will be tested with the Shapiro-Wilk test. Continuous variables will be compared between groups with either the unpaired t-test or the Mann-Whitney U test depending on distribution. Individual AAA growth (based on repeated AAA diameter measurements) and the evolution of serum levels of cytokines and proteases will each be analysed with linear mixed-effects models to estimate the slope of temporal change (ie, the evolution through time). The linear mixed-effects model that estimates the slope for the evolution of each biomarker will also adjust for potentially relevant covariables including but not limited to sex, age and cardiovascular comorbidity. A forward stepwise selection will be used to select only those covariables that were significant in univariable analysis. Finally, correlations coefficient will be estimated between the slope of AAA progression and the slope of each biomarker. Freedom from AAA rupture and all-cause mortality will be estimated with the Kaplan-Meier method, while joint modelling will be used to assess the association between the evolution of serum levels of proteases and cytokines and AAA rupture and all-cause mortality. A joint model will be performed per biomarker. In order to assess the association, joint modelling combines linear mixed-effects models for the estimation of slope of temporal change per biomarker with Cox regression for the analysis of freedom from AAA rupture and all-cause mortality, in order to estimate HRs. The estimated slope and value of the studied biomarker will be added as covariables in each joint model. Furthermore, both models will be adjusted for potentially relevant covariables, including but not limited to sex, age, most recent AAA diameter and cardiovascular comorbidity using the same selection procedure. In addition, AAA growth instead of the most recent AAA diameter will be analysed in a separate multivariable joint model. In all analyses, a p value of <0.05 will be considered statistically significant, including the covariable selection procedure.

AAA, abdominal aortic aneurysm; PARIS, Predicting aneurysm growth and rupture with longitudinal biomarkers.

In general, biobanks in the Netherlands do not fall within the scope of the WMO. To be eligible for assessment under WMO, the formulation of a specific research question is required. However, specific research questions are often not present at the moment of biobank initiation.^28^ Yet, the submission of the AAA bank together with the PARIS study (that contains a specific research question) enabled approval of the combined project within the scope of the WMO. This approval ensures that the AAA bank adheres to the highest legal and medical ethical standards and that participation of other future centres can be realised using the existing procedures of the WMO. Because of this design, all participating patients sign two informed consent forms—one for the biobank and one for the PARIS study (see online appendix 1–6 for English versions of the forms). By consenting to the AAA bank and signing its consent form, patients consent to the collection and storage of their biomaterials and data and to future analyses of it for research about AAA. Any significant modification to the protocol that may impact patient safety or the conduct, design or analysis of the study requires formal amendment to the protocol. These will need to be approved by the Medical Ethics Board and the Biobank ethics Board of Amsterdam UMC (University of Amsterdam).

To accommodate patients with different views on data collection, participants can refuse collection of DNA and the sharing of their data with foreign and/or commercial parties. All collected data and biomaterials will be stored for a maximum of 50 years. When a participant decides to withdraw from the AAA bank, all stored biomaterials and data will be destroyed or deleted. When reasonably possible, this is also done with materials that are sent out for a specific study.

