Recent studies focused on biomarker research to find early disease markers and potential targets for pharmacological treatment. Promising circulating biomarkers included markers of matrix turnover (matrix metalloproteinases), markers of inflammation (interleukins and C reactive protein) and markers of lipid metabolism (lipoproteins).^7–9^ Unfortunately, to date, none of these biomarkers have found their way to clinical practice. This is mostly due to their low prognostic value for AAA progression and because many studies have not corrected for factors such as smoking or comorbidities.^8^ The same applies to new imaging biomarkers such as ^18^F-fluoro-deoxy-glucose or biomechanical markers such as peak wall stress and wall shear stress.^10–12^

To better understand AAA pathophysiology and its natural course, it is imperative to combine studies with biomarkers, imaging markers and longitudinal data. To that end, a multicentre databank, biobank and imagebank has been established in the Netherlands: the ‘*Pearl Abdominal Aortic Aneurysm*’, hereafter referred to as the AAA bank. The aim of this project is to facilitate future studies on AAA. It is part of the Dutch Parelsnoer Institute (PSI), which facilitates uniform biobanking in all eight university medical centres (UMCs) in the Netherlands.^13^ The systematic collection of clinical data, biomaterials and imaging data will enable a diverse range of studies on patients with AAA. The AAA bank will especially focus on patients with a small AAA to collect longitudinal data early on in the development of AAA.

The first proposed study that will be carried out with the collected biomaterials is the ‘Predicting aneurysm growth and rupture with longitudinal biomarkers’ (PARIS) study. The PARIS study aims to determine the association between AAA progression and the evolution of serum levels of proteases and cytokines.

The scientific aims of the AAA bank are: (1) to gain insight in the pathophysiology and natural history of AAA; (2) to gain more knowledge about the rupture risk of AAA; and (3) to evaluate and improve treatment of patients with an AAA. Future studies with data from the AAA bank must adhere to these scientific aims.

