Patient information	Study number, year of birth and survival status including cause of death.
Informed consent	Status of informed consent (given or withdrawn), date of informed consent and individual patient decisions with regard to additional consent options.
Living situation	For example, independent or assisted living.
Current aneurysm state	For example, asymptomatic, acute or postoperative status.
First occurrence comorbidity	This eDCS contains a predefined list of comorbidities. Only if a participant has any of these comorbidities will this be registered, including the initial date of diagnosis. The list includes: hypertension, COPD, idiopathic lung fibrosis, peptic ulcer, diabetes mellitus, hypothyroidism and hyperthyroidism, hepatitis, portal hypertension, liver cirrhosis, any other liver disease, peripheral arterial disease, intracranial aneurysm, popliteal aneurysm, any other aneurysm, connective tissue disease, hypercholesterolaemia, carotid artery disease, renal dysfunction, renal disorders, ischaemic heart disease, heart failure, heart arrhythmia, heart valve disorders, any other cardiac disorder, haemiplegia or paraplegia, dementia and AIDS. Free-text descriptions can be provided for cases with an ‘any other’ comorbidity as mentioned above.
Family history	Registration of each known family member with (a history of) aortic aneurysmal disease and if known, at what age and whether there was an aortic rupture.
Social history	Marital status, employment status and educational status.
Initial aneurysm characteristics	Pathogenesis and type of AAA, status of AAA at time of inclusion, date of initial diagnosis and shape of AAA.
Comorbidity status	Status of a predefined list of comorbidities. This will be registered if this is known at the time of a visit to the department of vascular surgery. The list includes: COPD, diabetes mellitus (eg, dependency on insulin), peripheral arterial disease (eg, Fontaine classification), renal dysfunction, angina pectoris and heart failure.
Medication	This eDCS contains a predefined list of medications. Only pills and injections will be registered. If a medication is not included in the list, it will be added via a free-text description. Dosage will be registered for cardiovascular medications. The list includes: all types of cardiovascular medications, diabetes mellitus medication, corticosteroids, immunosuppressive medication and benzodiazepines.
Intoxications	Nicotine and alcohol use.

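### Confounders in the PARIS biomarker analyses are chosen by p-value and none, smoking included, is forced in, so associations can stay confounded

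*Protocol article*

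**What the plan says.** All of this is in the protocol article, Ethics and dissemination, Table 5, Statistical analysis, unless stated otherwise.

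- **Growth analysis.** Diameter growth and each biomarker get a linear mixed-effects model. Adjustment is described for one of the two: "The linear mixed-effects model that estimates the slope for the evolution of each biomarker will also adjust for potentially relevant covariables", with the list given as "including but not limited to sex, age and cardiovascular comorbidity". No covariables are stated for the growth model. The last step is that "correlations coefficient will be estimated between the slope of AAA progression and the slope of each biomarker".
- **Selection rule.** "A forward stepwise selection will be used to select only those covariables that were significant in univariable analysis". The threshold is the inferential one: "a p value of <0.05 will be considered statistically significant, including the covariable selection procedure".
- **Joint models for rupture and mortality.** There is one model per biomarker, and the rule above is applied again: "both models will be adjusted for potentially relevant covariables, including but not limited to sex, age, most recent AAA diameter and cardiovascular comorbidity using the" (at this point the sentence refers back to that rule).
- **Background.** The Introduction explains the failure of earlier biomarkers partly by the fact that "many studies have not corrected for factors such as smoking or comorbidities". It also lists smoking among the known determinants of AAA. Table 3 records "Nicotine and alcohol use" under Intoxications.

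**The concern.** A significance screen is not a rule for choosing confounders. Whether a variable confounds depends on its relation to both biomarker and outcome, not on whether its own test passes 0.05 in this sample. Four consequences follow.

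1. Any covariable can be removed by a p-value, including smoking and comorbidity, the two that the article faults others for omitting.
2. The rule is applied to each biomarker's model, so two biomarkers can be adjusted for different sets and their results are then not comparable.
3. P-values and intervals from the final model take no account of the selection and are too optimistic.
4. In the rupture models, stepwise selection is unstable if there are few events.

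The study aims at weak correlations (target r = 0.16), so even modest confounding matters. A biomarker that only tracks smoking could be read as a marker of growth.

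**Working it through.** **Inputs.** From the article: planned n = 750, currently enrolled n = 161, target r = 0.16, α = 0.05 (taken as two-sided). The article gives no confounder strength, rupture rate or visit count, so those below are assumptions. It also gives no figure on confounding to reproduce. Whether 750 follows from r = 0.16 is a separate question and is not used here.

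**1. How often does the screen keep a confounder?** Let ρ be the confounder's correlation with the biomarker slope. Then P(keep) ≈ Φ(atanh(ρ)·√(n−3) − 1.96).
- n = 750, ρ = 0.05: 0.0500 × 27.33 = 1.37, so Φ(−0.59) = 28%.
- n = 750, ρ = 0.10: 0.1003 × 27.33 = 2.74, so Φ(0.78) = 78%.
- n = 161: 10% and 25% by simulation.

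Weak confounders are therefore often dropped, above all in an early analysis.

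**2. What if a confounder is never adjusted for?** With correlation 0.3 on both slopes, the spurious r is 0.3 × 0.3 = 0.09, and 68% of tests at n = 750 are falsely positive. With 0.4 on both, r = 0.16, which equals the target effect, and 99% are falsely positive. For a binary confounder with 40% prevalence shifting both slopes by c SD, r = 0.24c²/(1 + 0.24c²):
- c = 0.3: 0.0216/1.0216 = 0.021, false positives 9%.
- c = 0.5: 0.06/1.06 = 0.057, false positives 34%.

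**3. The same confounders under the planned rule, if the screen tests the slope.** The binary confounder's correlation with the biomarker slope is √(0.24c²/(1 + 0.24c²)), that is 0.145 to 0.238. At n = 750 it is kept in 98–100% of runs; type I error is 4.1–4.4% and mean r about 0. Continuous confounder, 4,000 replicates, n = 750, no true association:

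| Correlation with biomarker / growth slope | Kept | Type I error, unadjusted | Type I error, planned rule |
|---|---|---|---|
| 0.05 / 0.3 | 28% | 6.7% | 4.7% |
| 0.10 / 0.3 | 78% | 13.2% | 4.2% |
| 0.30 / 0.3 | 100% | 68.4% | 4.2% |

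Six weak confounders together give roughly 6–8%. That range depends on the strengths assumed.

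**4. Does leaving the growth slope unadjusted add bias?** No. When the confounder is fully removed from the biomarker slope, mean r is about 0 and type I error is 2–4% with growth unadjusted.

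**5. Does the form of adjustment matter?** Mixed models, n = 750, 5 visits, confounder correlated 0.4 with both slopes, no true association, 12 replicates. Mean slope correlation:
- no adjustment: 0.150
- main effect only: 0.133
- main effect plus confounder-by-time: 0.001

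The SD between replicates is about 0.03, so the standard error of each mean is about 0.03/√12 = 0.009. A screen that tests only the level also loses strong slope confounders. Under one set of assumed variances, a confounder correlated 0.4 with the biomarker slope was kept in 29–37% of runs at n = 750; that figure moves with the variances.

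**6. Rupture events.** Assumed rate 0.25–1% per year and 2–6 person-years each: 750 × 0.0025 × 2 = 3.75, up to 750 × 0.01 × 6 = 45.

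**The case against.** The strongest reply is that the rule does little harm at the planned size. A reader might infer from step 2 that the plan carries a 9–34% false-positive rate. The documents do not support that: those rates belong to a confounder that is never adjusted for, and step 3 shows that the same confounder is almost always kept at n = 750, with about 4% type I error. This objection stands, provided that the screen tests the slope.

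A reader might also infer that the unadjusted growth slopes confound the correlation by themselves. They do not (step 4). Nor does the lack of stated adjustment extend to the joint models, where both parts are adjusted, and the article's Statistical analyses section offers multivariable mixed-effects models for growth.

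Third, smoking is not excluded, since both covariable lists are open-ended. The article also does not say that covariables enter as main effects only. That reading comes from silence, and such detail may sit in the full protocol or analysis plan. So smoking omitted and main-effect-only adjustment are possibilities to close off, not stated errors. It would also go too far to say that the plan simply repeats the earlier studies' flaw: it does plan adjustment and names cardiovascular comorbidity.

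Finally, the rupture count is wholly assumed. The article gives no rate and allows up to 10 years of follow-up.

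What remains is the selection rule itself. The article states it outright, so it is not a detail left to another document.

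**Conclusion.** The point holds in a limited form. Table 5 fixes a p-value rule under which any confounder can be dropped, and no covariable is protected. Associations can stay confounded, adjustment sets can differ between biomarkers, and post-selection inference ignores the selection.

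The bias from the screen alone is modest at 750 if it tests the slope: negligible for one strong confounder, and roughly 6–8% type I error for several weak ones. It could be much larger in two cases that the article leaves open. If smoking is never a candidate and correlates 0.3–0.4 with both slopes, the spurious r is 0.09–0.16. If covariables enter only as main effects, most of the spurious correlation remains (0.133 of 0.150). Instability in the rupture models is a concern only if ruptures prove few. All sizes rest on assumed strengths, not on trial data.

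The change should be made, because a better rule is available at almost no cost.

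**What to change.** - Replace the selection rule with one prespecified set, chosen on subject matter, forced in and identical for every biomarker: age, sex, smoking, cardiovascular comorbidity, diabetes and relevant medication.
- Enter it with covariable-by-time terms in the biomarker slope model. For consistency, preferably use the same set in the growth model.
- Use baseline diameter as a growth covariable only if that measurement is not also part of the outcome; otherwise the same error-prone value stands on both sides.
- In the rupture joint models, restrict the forced set to what the observed events support, or use penalisation.

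**Cost.** A few degrees of freedom, which is negligible at 750, and no extra patients. Table 3 already covers nicotine use, comorbidity including diabetes, medication and year of birth. It does not list sex, which Table 5 names as a covariable, so its capture should be confirmed. The Ethics and dissemination section requires a formal amendment, approved by both ethics boards, for significant changes to the analysis. With 161 of 750 enrolled and no results reported, the set can still be prespecified.
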